### Standard of Care

The standard of care for PWID admitted to UAB Hospital with SIRI includes an Infectious Diseases and Addiction Medicine consultation [4]. Peer support staff meet with all SIRI patients daily during their admission with varying frequency, but peer support does not routinely extend beyond discharge. Over 125 SIRI cases are treated annually: skin, soft tissue, blood, and heart infections. Most have opioid use disorder (OUD), 30% have comorbid methamphetamine use [22, 23]. In a recent survey of 20 PWID at UAB, 50% reported condomless sex and 75% reported sharing injection materials, yet none received PrEP Only 37% were discharged with lifesaving medications for OUD, like buprenorphine [7].

### Intervention

This study will test two interventions. The SIRI Checklist will build on the existing standard of care for SIRI by adding a standardized reminder to offer MOUD, HIV risk assessment, and refer to appropriate community-based care. SIRI Checklist was inspired by the iCARE checklist, developed for endocarditis in PWID, but is applicable for all PWID and will incorporate HIV prevention, harm reduction education, and linkage to care, including HCV treatment [5].

For participants who are randomized to receive the SIRI checklist, providers will receive instructions on how to insert a 5-item checklist into their documentation using a smart phrase text for ease of use and standardization (appendix 2). Because use of a checklist alone has been shown to change provider behavior, providers will not be required to perform any additional tasks other than daily documentation of the checklist. We anticipate that documentation of evidence-based services using a checklist reminder will increase the likelihood that participants will receive them.

The intensive peer intervention will include weekly calls to participants for 4 weeks following discharge. If participants do not respond, peers will make 3 attempts to reach participants at their preferred contact number.

### Recruitment

#### Eligibility Criteria

##### Inclusion Criteria:

We will include 60 PWID with serious injection related infections (SIRI) who are HIV negative, ≥ 18 years old and receiving care at UAB Hospital for each of the three aims.

##### Exclusion Criteria:

We will exclude those unable to provide informed consent due to acute illness or intoxication and those who are living with HIV in order to inform HIV prevention interventions.

#### Sampling and Recruitment Procedures

Participants will be recruited following hospitalization for SIRI at UAB Hospital. Our research coordinator will meet biweekly with the Addiction Medicine social worker and/or nurse practitioner, to identify eligible PWID who express interest in study participation. The research team member will then discuss the study with those who are eligible, and if the participant expresses interest, the informed consent process will be completed (appendix 3). We will provide phones for participants who do not have access to a phone. The participant will then complete the survey used to accomplish Aim 1. Following survey completion, the participant will be randomly sorted using a 2x2 Factorial Design, into one of the four groups: SIRI Checklist, SIRI Checklist + Enhanced Peer, Enhanced Peer, and Standard of Care. Randomization will be performed in advance using blocks of n = 4 and n = 8. A total of 60 participants will be recruited, 15 per group, which is in alignment with sample size guidance for pilot and feasibility studies [24]. For incentive, patients will receive a $30 gift card at enrollment, as well as a $30 gift card at the 3-month follow up (Fig. 2).

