To evaluate the transition to the main trial, we will utilize progression criteria around 1) recruitment and retention, 2) protocol adherence, 3) safety and adverse effects, and 4) signals of efficacy [14]. We will utilize the red, amber, green system for progression criteria [20]. (Fig. 1) For recruitment, we expect to encounter 3 to 4 eligible participants monthly, based on previous studies we have conducted within this population. Given that some of these individuals will refuse to participate in the study, we expect to enroll 2 to 3 participants each month. If we maintain recruitment of 2 or more patients per month, we expect to reach our goal of enrolling 60 participants (15 participants for each arm of the study) within 24 months. If recruitment falls below 2 patients per month, we will explore alternate methods for recruitment to improve recruitment rates. If recruitment stalls and no patients are recruited for more than two consecutive months, the trial will terminate. Retention will be determined by documenting the proportion of: participants who complete weekly calls with their peer, peer calls completed, and participants who complete the follow up survey at 3 months. The target retention rate for each of these rention progression criteria is 75% [21].

To ensure adherence to the study protocol, we will monitor patient documentation to determine whether the ShaPe “smart phrase” was utilized in patient notes. We expect that this smart phrase will be included in all participant documentation after implementation. If adherence to the study protocol falls below 80%, we will revisit the protocol with providers to determine whether further training or modifcations are necessary [21].

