### Analysis

To evaluate our primary aim, feasibility will be evaluated through time and number of eligible participants required for participant recruitment, participant retention, and completion rates. Acceptability will be evaluated through patient enrollment and provider survey responses towards the SIRI checklist and Intensive Peer.

As a secondary outcome, we will explore the participant data and summarize sociodemographic and clinical factors of participants using descriptive statistics (measures of central tendency, dispersion, and distribution) and confidence intervals. Clinical factors will include initiation of buprenorphine, PrEP, HIV and HCV screening, and referral to community care. Lastly, we will evaluate the provider survey data to identify overall trends in provider responses.

These results are planned for presentation at national conferences and inclusion in manuscripts for publication in high impact journals.

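### The pool of eligible patients behind the recruitment and acceptability measures is not fixed; if patients lost before research contact go uncounted, uptake is overstated

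*Protocol article*

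**What the plan says.** Three places in the protocol article bear on this.

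- **Sampling and Recruitment Procedures.** "Our research coordinator will meet biweekly with the Addiction Medicine social worker and/or nurse practitioner", and the purpose is "to identify eligible PWID who express interest in study participation". The next step is "The research team member will then discuss the study with those who are eligible, and if the participant expresses interest", after which consent is taken. Interest is therefore mentioned twice: once before research contact and once after.
- **Progression criteria (under Aim 2).** "we expect to encounter 3 to 4 eligible participants monthly". The article continues: "Given that some of these individuals will refuse to participate in the study, we expect to enroll 2 to 3 participants each month". Eligible here includes people who go on to refuse. The same text sets the recruitment trigger at 2 or more enrolled a month. It also says that if recruitment is too slow, the team will ask whether the population is large enough and, if so, how to identify candidates better.
- **Analysis.** For the primary aim, "feasibility will be evaluated through time and number of eligible participants required for participant recruitment", together with retention and completion. "Acceptability will be evaluated through patient enrollment and provider survey responses towards the SIRI checklist and Intensive Peer".

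The article writes out no enrolment ratio. One is implied by counting the eligible patients needed to reach the recruitment target.

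**The concern.** A measure of how many eligible patients it takes to recruit the sample, or of acceptability as shown by enrolment, needs a denominator that includes the unwilling. The recruitment procedure, read literally, identifies only those who have already shown willingness to a social worker or nurse practitioner. The forecast describes a wider pool, and the Analysis section does not choose between them.

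Two things are at stake. First, a larger trial would be planned from the recruitment yield seen here, and a yield calculated among interested patients would make that trial look easier to fill than it is. Second, the plan wants to diagnose slow recruitment. Without a count of all eligible patients, a small population, poor identification and early refusal are hard to tell apart.

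This is a matter of data capture. A denominator that was never recorded cannot be rebuilt by any later analysis plan.

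**Working it through.** **Inputs**
- Eligible per month: 3 to 4, midpoint 3.5 (progression criteria).
- Enrolled per month: 2 to 3, midpoint 2.5 (progression criteria).
- Target: 60 in 24 months (progression criteria).
- d, the share of eligible patients who decline to clinical staff or are not asked: not given. Assumed range 0 to 50%.

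**The plan's own figure.** 60/24 = 2.5 enrolled a month, which is the midpoint of the forecast, so the midpoints are used below.

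**Implied uptake.** 2.5/3.5 = 71%. Pairing low with low gives 2/3 = 67%, and high with high gives 3/4 = 75%. The extreme pairings are 2/4 = 50% and 3/3 = 100%. At the midpoints, enrolling 60 takes 60 × 3.5/2.5 = 84 eligible patients.

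**Effect of the filter.** Let E be all eligible patients and n those enrolled. If a share d is lost before research contact and not counted, the visible pool is E(1-d). Then:

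- observed uptake = n/[E(1-d)] = true uptake/(1-d)
- true uptake = observed uptake × (1-d)
- eligible patients needed for 60 = 60/true uptake

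Suppose the observed uptake is 71%:

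| Assumed d | Overstatement 1/(1-d) | True uptake | Eligible needed for 60 |
|---|---|---|---|
| 0% | 1.00 | 71% | 84 |
| 10% | 1.11 | 64% | 93 |
| 20% | 1.25 | 57% | 105 |
| 30% | 1.43 | 50% | 120 |
| 40% | 1.67 | 43% | 140 |
| 50% | 2.00 | 36% | 168 |

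The factor is never below 1, so the error can only be upward. It is zero if d = 0 or if the lost patients are counted.

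**What is not touched.** The trigger of 2 or more enrolled a month, and the rule on consecutive months without recruitment, are counts with no denominator.

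**The case against.** The strongest reply is that the article describes how patients are found and does not say that decliners go unrecorded. A screening log is the kind of detail an article leaves to the full protocol, Table 1 lists an eligibility screen before consent, and the flow diagram is not available here. That stands. A reader might infer that early decliners certainly never enter the count and that the outcome is certainly biased; the article supports only the conditional statement.

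A reader might also infer that uptake would look good whatever the refusal rate. That goes too far. The discussion with the research team is a second point at which patients can refuse, and those refusals are visible.

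A third inference would use the site caseload. Over 125 SIRI cases a year is about 125/12 = 10.4 a month, and setting 2 to 3 enrolments against roughly 10 suggests that uptake is overstated two- or threefold. The caseload does not support that. It counts cases rather than eligible people, so the gap down to 3 to 4 a month also reflects repeat admissions, patients unable to consent, those living with HIV and those missed between meetings. It does not estimate d.

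Finally, acceptability does not rest on enrolment alone. Provider surveys contribute, and exit interviews ask participants about the checklist. The interviews reach only people who enrolled, however, so they cannot show why others did not.

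What survives is that the recruitment procedure and the forecast describe different pools, and the Analysis section does not say which one it uses.

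**Conclusion.** The point holds as a conditional one. The article pre-selects on interest in its recruitment procedure, includes refusers in its forecast, and leaves the denominator of its recruitment and enrolment-based acceptability measures open. If patients lost at the first step are not counted, uptake is overstated by 1/(1-d). With d assumed between 10% and 50% the factor is 1.11 to 2.00, and an observed 71% corresponds to a true 64% to 36%. The size rests entirely on that assumed range and on treating the planning midpoints as the observed result; the article offers no estimate of d.

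A reader might conclude that the decision to progress on recruitment is itself compromised. The trigger stated in the text is a monthly count of enrolments and is unaffected. The harm is confined to the feasibility and acceptability measures in the Analysis section and to the planned diagnosis of slow recruitment. The change is worth making because it is cheap and the missing count cannot be recovered later. If a log of all eligible patients already exists, a sentence saying so, with the denominator stated, settles the matter.

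**What to change.** - **Sampling and Recruitment Procedures.** Have the social worker or nurse practitioner report, at the existing biweekly meeting, every SIRI admission that meets the Inclusion and Exclusion Criteria, regardless of interest. Add a one-line reason when a patient was not asked or was not interested. Record counts only, with no identifiers for those who decline.
- **Analysis.** Define uptake as enrolled divided by all eligible, and report the number at each step: eligible, asked, interested, consented, randomised. Say that the recruitment measure and the enrolment part of acceptability both use this denominator.

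The cost is a tally sheet at a meeting that already takes place, a few lines of protocol wording, and a reported uptake that will be lower than one calculated among interested patients only.

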### Data Sources

We will collect data on stigma, HIV awareness and risk behaviors via electronic surveys; results will be stored in a RedCap database [25]. We will obtain data on sociodemographics and clinical factors, like type of infection and HIV and HCV test results, using data extracted from the Electronic Medical Record (EMR) and managed in a RedCap database. Prescription data and healthcare utilization data will also be obtained from the EMR. We will extract outcomes related to linkage to prescription for PrEP and/or MOUD on discharge, and attendance at provider visit(s) related to HIV and/or addiction services following hospitalization. Data extraction will be limited to services provided in the UAB health system.

Participating providers who serve PWID will be asked to complete a standardized survey of the study and intervention in order to determine the study feasibility and identify opportunities to improve.

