The use of a “checklist” can improve provider awareness, best practice, and clinical outcomes for seriously ill patients [12, 13]. Checklists are low cost and low technology reminders to providers to ensure they deliver evidence-based services to a target population. Together with a team of physicians, social workers, and peer recovery coaches, we developed a SIRI Checklist to act as a standar[14]dized reminder to offer these patients screening for HIV and HCV, medication for opioid use disorder (MOUD), consider HIV pre-exposure prophylaxis (PrEP) and referral to appropriate community-based care. Our team also formalized an Intensive Peer Intervention whereby PWID would be contacted weekly in the month following discharge to provide support, adherence reminders, and serve as a resource related to community addiction services.

We hypothesize that it is feasible to provide a SIRI checklist and an intensive Peer support to hospitalized PWID. Further, we anticipate that the SIRI Checklist and Intensive Peer Intervention will increase use of hospital-based services (HIV, HCV screening, MOUD) and linkage to community-based care: PrEP prescription, MOUD prescription, and related outpatient visit(s).

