## Methods/Design

### Setting

We will recruit 60 participants who are hospitalized for SIRI at the University of Alabama at Birmingham (UAB) Hospital to participate in this pilot clinical trial. The UAB Health system, anchored by the 1157-bed tertiary care center of UAB Hospital, is the largest in the state, and it provides care for PWID referred from other health systems across the Southeast [4].

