#### Aim 2: Secondary Patient-Centered Outcomes:

In Aim 2, we will use validated tools to survey participants on specific substance use and behaviors, stigma, HIV risk, and preferences around care delivery. Specifically, we will use the 14-item Behavioral Risk Assessment for Infectious Diseases (BRAID) scale, which queries drug use and sexual behaviors while using drugs, and the Substance Use Stigma Mechanisms Scale (SU-SMS), an 18-item validated, theoretically-based assessment [16, 17]. The first component includes surveys that will be administered electronically via tablet in private hospital rooms to reduce social desirability bias (appendix 1) [18]. The second component will be a 3-month follow up survey to assess use of PrEP, addiction treatment, and healthcare utilization. These sessions will last 30 minutes and 45–60 minutes, respectively. Each survey session will include a $30 incentive for patients.

Preliminary treatment outcomes will be explored using hospital data, such as rates of screening for HIV and receipt of HIV prevention (PrEP).

Traditionally, research on PWID is limited by a lack of retention beyond 30 days. To test the feasibility of retaining patients in the study for 3 months, we will work with a professional company, Community Tracking Service (CTS), with expertise in identifying and conducting exit interviews in persons who use drugs as part of extramurally funded research. After three attempts to reach study participants for the exit interview, our study staff will notify our partners at CTS who will then attempt to reach the participant up to one-month post-referral. These attempts may be over phone or in-person at locations identified by participants as part of their intake survey. Open-ended questions will solicit feedback on specific aspects of the checklist or delivery that need to be addressed, edited, or removed before a subsequent randomized controlled study [19]. For participants who do not complete the exit interview, we will review the UAB and coroner data to determine if hospitalized or deceased.

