** *Secondary Outcome variables* **				
*Number of prescriptions for PrEP*			X	
*Number of prescriptions for medications for MOUD*			X	
*Number of outpatient visits attended related to HIV &/or addiction services following hospitalization.*			X	

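### Post-discharge visits (and later prescriptions) are taken from UAB-only records although the hypothesis is linkage to community care; the planned 3-month survey is not tied to this outcome

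*Protocol article*

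**What the plan says.** Data Sources assigns this information to the EMR: "Prescription data and healthcare utilization data will also be obtained from the EMR". The outcomes to be extracted are PrEP and/or MOUD prescriptions on discharge and "attendance at provider visit(s) related to HIV and/or addiction services following hospitalization". The section then sets the limit: "Data extraction will be limited to services provided in the UAB health system". Surveys appear in the same section as the source for stigma, HIV awareness and risk behaviours, not for visits.

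Table 1 lists, in its 3-month follow-up column, the numbers of PrEP and MOUD prescriptions and "Number of outpatient visits attended related to HIV &/or addiction services following hospitalization". It names no source.

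On where care is likely to take place, Setting says of the UAB system that "it provides care for PWID referred from other health systems across the Southeast". Under Intervention, the checklist reminds providers to "refer to appropriate community-based care". In Background, the peer is to "serve as a resource related to community addiction services". The hypothesis in the Abstract and Background concerns linkage to community-based care, measured by PrEP prescription, MOUD prescription and related outpatient visits.

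The Aim 2 section also plans "a 3-month follow up survey to assess use of PrEP, addiction treatment, and healthcare utilization". The Abstract (Methods) says that clinical outcomes such as testing and MOUD and PrEP prescriptions will draw on surveys and EMR data together. The progression-criteria text under Aim 2 says that the data on efficacy signals will come from provider documentation and the 3-month survey.

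**The concern.** The hypothesis is about care in the community, but the only source expressly assigned to visit attendance sees one health system. A participant who goes home and attends an addiction clinic there contributes zero visits to a UAB-only count. The same holds for a prescription written elsewhere after discharge.

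If the loss were equal in all arms, the observed difference would shrink. It need not be equal. Both interventions encourage use of community services, so the arm that succeeds best may have the largest share of its care out of sight. An exploratory comparison of visits could then show little or nothing where there was a real effect, and that comparison may inform the design of the larger trial.

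**Working it through.** **Which outcomes are exposed**

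| Outcome | Where it occurs | Visible in the UAB EMR? |
|---|---|---|
| Inpatient HIV and HCV screening | UAB | Yes |
| PrEP or MOUD prescription on discharge | UAB | Yes |
| Referral to community care | UAB, at discharge | Yes, if documented |
| PrEP or MOUD prescription after discharge | Any provider | Only if at UAB |
| HIV or addiction visit after discharge | Any provider | Only if at UAB |

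Only the last two rows are at issue.

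**Which source the protocol article assigns**

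- Abstract: survey and EMR together. Testing, MOUD and PrEP are named; visits are not.
- Progression criteria: provider documentation and the 3-month survey. The examples are screening, MOUD prescriptions and PrEP referrals; visits are not named.
- Aim 2: the 3-month survey covers PrEP use, addiction treatment and healthcare utilisation.
- Data Sources: prescriptions, utilisation and visit attendance from the EMR, UAB services only.

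So the survey collects relevant information, but the one section that names a source for visits leaves it out.

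**Illustration of size**

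The documents give no linkage rates by arm and no share of care outside UAB. What follows is assumption, not estimate. The article's own figures are the sample size (4 × 15 = 60, so 30 v 30 for each factor) and the 75% target for 3-month survey completion.

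Let p be true linkage and s the share of linkage visible at UAB. Observed linkage is p × s.

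*Equal capture.* The observed difference is s × (true difference). With 25%, 50% or 75% of linkage outside UAB, s = 0.75, 0.50 or 0.25. Assuming true linkage of 35% without and 55% with the intervention (20 points):
- s = 0.75: 26.25% v 41.25%, difference 15 points
- s = 0.50: 17.5% v 27.5%, difference 10 points
- s = 0.25: 8.75% v 13.75%, difference 5 points

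*Lower capture in the intervention arm, same true rates.*
- 75% v 50%: 0.35 × 0.75 = 26.25%; 0.55 × 0.50 = 27.5%; difference about 1 point
- 50% v 30%: 0.35 × 0.50 = 17.5%; 0.55 × 0.30 = 16.5%; difference about −1 point

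*EMR plus survey, all randomised.* Assume that 75% complete the survey, that completion is unrelated to linkage, and that completers report all outside care. Capture is s + (1 − s) × 0.75, which is 93.75%, 87.5% or 81.25%. The 20-point difference is then seen as about 19, 17.5 or 16 points.

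**How non-completers should be handled**

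One possible rule counts a non-completer with a UAB record as linked and sets the others to missing. Assume 50% true linkage, half of it at UAB, and 75% completion unrelated to linkage:
- Linked completers: 0.75 × 0.50 = 0.375
- Non-completers with a UAB record: 0.25 × 0.50 × 0.50 = 0.0625
- That rule gives (0.375 + 0.0625) / (0.75 + 0.0625) = 0.4375 / 0.8125 = 54%, which is too high.
- Completers only: 0.375 / 0.75 = 50%
- Bounds for all randomised: 43.75% if the remaining non-completers (0.25 − 0.0625 = 0.1875) are counted as not linked; 0.4375 + 0.1875 = 62.5% if counted as linked.

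Under these assumptions the completers-only estimate recovers the true value, and the bounds show what non-completion could do to it.

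**The case against.** The strongest reply is that the protocol does not rely on UAB records alone. The Abstract and the progression criteria both bring in surveys, and the Aim 2 survey is not restricted to UAB services. The UAB limit is an openly stated limit on record extraction. How two sources are merged is the kind of detail that a condensed article may leave to a fuller document. The efficacy-signal examples are mainly things done at UAB, and visits are not among them. The outcomes are exploratory, with 15 per group and a descriptive analysis.

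Much of this stands. It rules out saying that linkage as a whole is measured only at UAB, and it confines the problem to visits and later prescriptions. It does not remove the problem. Data Sources states the source for visits and its limit, so this is something the article fixes, not something it leaves out. The two sections that call for surveys do not mention visits. For people who miss the exit interview, the planned check of UAB and coroner data is meant to establish hospitalisation or death, and would not show outside clinic care.

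A further objection is that using the survey may bring its own imbalance: weekly peer calls could raise 3-month survey response in the peer arms. That is a fair caution, and it is why completion by arm has to be reported with the result.

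**Conclusion.** The point holds in a limited form. Followed as written, Data Sources will undercount post-discharge visits, and any prescriptions written after discharge, for participants treated outside UAB. The undercount may differ by arm, because the interventions direct people to community services; the documents neither show nor exclude this. Its size cannot be derived from them. Under the equal-loss assumption, the EMR-only difference is 75%, 50% or 25% of the true one; under assumed unequal loss it can vanish or turn slightly negative.

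Three stronger readings are tempting and are not supported:
- A reader might infer that absence from UAB records is scored as failure to link. No scoring rule is stated; a UAB-only count simply records zero.
- A reader might infer that the efficacy signal for the main trial will be wrong. The signals named are largely visible at UAB, and the survey is one of their stated sources.
- A reader might take the 37% in Standard of Care as a baseline for community linkage. It is the share discharged on medication for opioid use disorder, which UAB records capture, so it is not used here.

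The primary feasibility outcomes do not depend on any of this. The change is worth making because the survey that would largely repair the gap is already planned.

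**What to change.** Reconcile Data Sources and Table 1 with the Abstract, the Aim 2 survey description and the progression criteria, as follows.

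1. Define post-discharge linkage as any HIV or addiction visit, or PrEP or MOUD after discharge, that is either reported in the 3-month survey for any provider or found in the UAB EMR.
2. Estimate it among survey completers.
3. Give bounds for all randomised participants: count non-completers with no UAB record first as not linked, then as linked.
4. Report survey completion by arm beside the result.
5. Report the EMR-only counts in Table 1 separately, labelled as UAB-delivered care.

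Discharge prescriptions, referrals and inpatient screening can stay on the EMR.

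The cost is a change of wording and some extra tabulation, since the survey is already planned to cover these areas. The drawbacks are reliance on self-report for care outside UAB, and a comparison that may be affected if survey completion differs between arms.
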